## Abstract

**Background and Aims:**

Inflammatory bowel disease (IBD) is a chronic inflammatory gastrointestinal tract disease subdivided into Crohn's disease (CD) and ulcerative colitis (UC). There is currently no cure for IBD, and individuals with IBD frequently experience a lower health‐related quality of life (HRQOL) than the general population. Gamification has become an increasingly popular topic in recent years. Adapting game design concepts to nongaming contexts represents a novel and potential approach to changing user engagement. This study will be conducted with the aim of evaluating the effect of a gamified mobile‐based self‐management application on disease activity index, quality of life, and mental health in adults with IBD.

**Methods:**

A multicenter, parallel, two‐arm, exploratory randomized controlled trial with a 6‐month follow‐up per patient will be designed to compare the impact of the gamified mobile‐based tele‐management system on primary and secondary health outcomes and outpatient visits in 210 patients with all types of IBD which are divided equally into a control group with standard care and an intervention group which will use the developed mobile application named *MY IBD BUDDY*. All patients will attend study visits at baseline, 12 and 24 weeks, and routine IBD clinic visits or telephone consultations based on randomization group assignment. Disease activity or disease activity index, mental health (anxiety and depression) symptoms, quality of life, self‐efficacy, and IBD‐specific knowledge will be measured at baseline with two follow‐ups at 12 and 24 weeks.

**Conclusions:**

In sum, the outcomes of our trial will demonstrate the impact of the gamified mobile‐based self‐management system on disease activity, quality of life, and anxiety and depression by means of interactive care and patient empowerment.

**Trial Registration:**

IRCT: IRCT20200613047757N1. Registered November 16, 2021. Prospectively registered and visible at OSF (https://doi.org/10.17605/OSF.IO/AWFY9).

## INTRODUCTION

1

### Background

1.1

Inflammatory bowel disease (IBD) is a chronic inflammatory gastrointestinal tract disease subdivided into Crohn's disease (CD) and ulcerative colitis (UC).^1^ It is caused by an exaggerated immune system reaction to a normal stimulus, such as food and intestinal flora, in genetically susceptible individuals.^2^ In North America, UC has 2.2–19.2 instances per 100,000 person‐years, while CD has 3.1–20.2 per 200,000. An extensive insurance claims analysis found 238 and 201 cases of adult UC per 100,000 Americans. North America and Europe have more IBD than Asia or Africa. Up to 25% of individuals acquire IBD by adolescence. A second 10%–15% peak developing IBD beyond 60 suggests a bimodal distribution. According to a considerable investigation based on insurance claims, the prevalence of UC in adults in the United States was 238 per 100,000 and 201 per 100,000. IBD is more prevalent in North America and Europe than Asia and Africa.^3^

### IBD self‐management

1.2

Self‐management is an interactive and evolving process that captures the complexities of coping with chronic illness within the context of daily life.^4^ It involves acquiring skills that help individuals effectively manage their chronic conditions on a day‐to‐day basis. self‐management involves three main tasks^5^: dealing with illness‐related challenges, addressing everyday life responsibilities, and reflecting on one's life experiences. Building upon this definition,^6^ identified five essential self‐management skills: problem‐solving, decision‐making, resource utilization, establishing partnerships with healthcare professionals, and taking proactive steps to manage one's health. There is currently no cure for IBD, and individuals with IBD frequently experience a lower health‐related quality of life (HRQOL) than the general population.^7^ An increasing corpus of research indicates that effective self‐management contributes to enhanced health outcomes, including pain, disability, and healthcare utilization, in various populations. However, limited is known about the different parts and effects of self‐management among IBD patients.^8^

### Gamification conceptual

1.3

Gamification has become an increasingly popular topic in recent years. Adapting game design concepts to nongaming contexts represents a novel and potential approach to changing user engagement.^9^ Gamification design benefits numerous fields, including e‐commerce, education, and healthcare.^10^ Combining psychology and technology to achieve business objectives, however, the function of technology in gamification has evolved significantly. Mobile health is the next suitable surge of technologies for modulating patient involvement and activities, reshaping gamification design in health care due to its unique technological capabilities.^11^ Combining the concept of a gamified mobile‐based self‐management system with IBD could result in the development of a mobile application designed to aid individuals with IBD in more effectively managing their condition.^12^

The present platform could be used in various fields such as Social Support Community Engagement, Symptom Management, Goal Setting and Progress, Education and Resources, and Tracking or Reminders.^13^ By gamifying the self‐management manipulation, IBD individuals may feel inspired, involved, and empowered to take an active role in their health management, resulting in improved symptom control, and improved health.^14^ To our knowledge, this research is the first study that has focused on the design of self‐care and monitoring systems for IBD patients with gamification techniques.

This study is a preliminary research to provide an explanation of the research protocol, offering a step‐by‐step approach and its methodology, and in the second paper, the results will be analyzed and reported.

## METHODS

2

### Objective and aims

2.1

The main goal of this study is to evaluate the efficacy of a gamified mobile‐based self‐management intervention system in reducing disease activity index and improving mental health and quality of life in adults with IBD compared to standard routine care. The authors hypothesize that the use of this new intervention system will result in lower disease activity index, improved anxiety and depression symptoms, improved quality of life, increased self‐efficacy, and IBD‐specific knowledge. The hypothesized mechanism of action of the self‐management intervention on health outcomes is summarized in Figure 1. This conceptual model is based on Murray et al.'s research.^15^

**Figure 1 hsr22109-fig-0001:**
[figure not shown]
Conceptual model outlining the hypothesized mechanism of action of the IBD adult patients charge: managing IBD gamified mobile‐based intervention. IBD, inflammatory bowel disease.

### Study setting

2.2

Adult IBD patients will be recruited in person from three Iranian adult gastroenterology and Hepatology centers. A local research coordinator will explain the study to eligible patients and obtained written consent.

### Eligibility criteria

2.3

#### Inclusion criteria

2.3.1

(1) Participants must have been diagnosed with IBD according to internationally accepted criteria at least 6 months before the start of the study, (2) age ≥ 18 years, (3) able to speak and read Persian (Farsi), (4) willing and able to provide written consent, and (5) familiarity with and access to an android smartphone or tablet, and internet.

#### Exclusion criteria

2.3.2

Patients meeting the following criteria are excluded from the study:
Inability to communicate with the research team and adherence to study requirements.Unwillingness to sustain participation.Pregnancy.Active perianal disease or anal fistula.Ileostomy, colostomy, pouch anastomosis, or ileorectal anastomosis.Pending or imminent surgery.Participation in another experimental study or educational interventions throughout patient enrollment.Uncontrolled and significant comorbidities or cognitive impairments.Patients with a hospital admission within 2 weeks before the study will be excluded for ethical reasons.

### Study procedure and design

2.4

In the present study, a gamified mobile‐based tele‐management system for patients with all types of IBD will be developed. To compare the impact of the gamified mobile‐based tele‐management system on health outcomes and outpatient visits in patients with all types of IBD, the authors will design a multicenter, parallel, two‐arm, exploratory randomized controlled trial with a 6‐month follow‐up per patient. IBD patients will be recruited from general practices and outpatient clinics after completing baseline questionnaires and providing informed consent. Subsequently, eligible patients will be randomly assigned to either (A) self‐management support through the use of the gamified mobile‐based tele‐management system (intervention group, MyIBD Buddy app), or (B) standard IBD care (control group). All patients will attend study visits at baseline, 12 and 24 weeks, and routine IBD clinic visits or telephone consultations based on randomization group assignment. Disease activity, anxiety and depression symptoms, quality of life, self‐efficacy, and IBD‐specific knowledge will be measured at baseline and during the 24‐week follow‐up. The Harvey–Bradshaw index (HBI) will measure disease activity among CD patients. Also, the disease activity among UC patients will be investigated using the simple clinical colitis activity index (SCCAI, also known as the Walmsley index). Notably, the Research Ethics Committee of Mashhad Faculty of Medical Sciences approved the current study in November 2021 (IR.MUMS.REC.1400.230). The trial prospectively registered is at IRCT (IRCT20200613047757N1) and visible at OSF (https://doi.org/10.17605/OSF.IO/AWFY9).

### Sample size

2.5

With a significance level of 5%, statistical power of 80%, a correlation coefficient of at least 0.3 between the scales, and three measurements of the results—once at baseline and twice after randomization—repeated measures analysis will be used to calculate the sample size. The results of relevant publications will be used as the foundation for the analysis of covariance (ANCOVA) for various indicators. The sample size was calculated using the Sampsi module and the minimum clinically important difference (MCID) effect technique in the Stata 2015 environment. Consequently and based on the enormous sample size available for the quality of life index and accounting for the likelihood of a 20% dropout for each of the three measurements of the outcome, the sample size for this research is 105 participants in each group and 210 participants will be recruited.

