### Statistical analysis

2.11

These models' adjusted intervention effects and 95% confidence interval and *p* values will be provided. Statistical significance will be determined by a two‐sided *p* value > 0.05. Statistical analysis will be conducted to understand the characteristics of patients with missing data.

Using SPSS's multiple imputation approach, missing data at the case level will be imputed. For the statistical analysis, SPSS V.22 will be used.

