#### Primary study analysis

2.11.1

The initial outcome analyses investigated mean disease activity measures within disease type at baseline and each of the measurement; repeated measures analysis of variance (ANOVA) will be used to compare the intervention groups and standard care at these time points. Also, repeated measures ANOVA will be used to compare each group's change from baseline at 12 and 24 weeks, within disease type. The two groups will be combined in the same analyses if a low variation is identified. Plots of mean outcome values in each group will be examined for indications of change patterns. Similar analyses will be used for quality of life and anxiety and depression scores by groups and for all participants.

Furthermore, the primary goal of these repeated measures analyses will be to detect differences between the intervention groups in patterns of change from baseline across the 6 months. Regression diagnostics will be examined to detect outliers, influential observations, and other deviations from assumptions for all models. To detect potential bias by analysis of only the collected data, participants with and without data at a given time will be compared to determine the baseline characteristics of those who did not provide complete data.

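### The sample size section names ANCOVA as the basis of the 80% power, but the primary analysis is a repeated measures ANOVA of change from baseline, which has less power at the planning correlation

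*Protocol article*

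**What the plan says.** Section 2.5 (Sample size) gives the planning inputs as "With a significance level of 5%, statistical power of 80%, a correlation coefficient of at least 0.3 between the scales", with the outcome measured "once at baseline and twice after randomization". It refers to a repeated measures calculation in Stata's sampsi module with an MCID effect. The one analysis method it names is ANCOVA: "The results of relevant publications will be used as the foundation for the analysis of covariance (ANCOVA) for various indicators". Quality of life is the outcome that set the number. After a 20% allowance for dropout the result is 105 per group, 210 in all. No SD is given.

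Section 2.11.1 (Primary study analysis) names repeated measures ANOVA. It compares the groups at the measurement times and also compares "change from baseline at 12 and 24 weeks, within disease type". It then states that "the primary goal of these repeated measures analyses will be to detect differences between the intervention groups in patterns of change" over the six months. Similar analyses are planned for quality of life, including for all participants together.

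Section 2.10 adds a multivariable linear regression. Its covariates are IBD subtype, baseline disease activity in two classes (remission or active), age, sex, disease duration, smoking and education. Section 2.11 says that adjusted effects, confidence intervals and p values will be reported. No section enters a participant's baseline quality-of-life score as a covariate.

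**The concern.** ANCOVA and change from baseline estimate the same arm difference in a randomised trial, but with different precision. ANCOVA removes only the part of the follow-up score that the baseline predicts. Subtracting the whole baseline when the correlation is low adds noise. An N that is just enough for ANCOVA is therefore too small for a change-score analysis at the same correlation.

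The mismatch affects the all-patient quality-of-life comparison on which the trial was sized, before any split by disease type. If N came from ANCOVA, an effect of the planned size could be missed almost half the time at r = 0.3, and a null result would still be reported from a trial described as having 80% power.

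**Working it through.** **Inputs from the article.** Alpha 5% (section 2.5), two-sided (section 2.11); power 80%; correlation at least 0.3; one baseline and two follow-ups; 105 per group; 20% dropout (all section 2.5). Table 1 gives 16 points as the clinically significant IBDQ change; section 2.5 does not say which value was used.

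**Assumptions.** One common correlation r between all pairs of visits, equal SD at each visit, and the same effect at 12 and 24 weeks. Section 2.5 speaks of "a correlation coefficient of at least 0.3 between the scales"; reading this as a between-visit correlation is an inference.

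**Step 1: can 105 be reproduced?** Not without an SD. The formula per group is n = 2 × (1.960 + 0.842)² × V × SD² / 16² = 2 × 7.849 × V × SD² / 256, where V is the variance factor of the method (step 2). Taking 105 × 0.8 = 84 evaluable per group:

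- ANCOVA (V = 0.56): implied SD about 49.5.
- Change from baseline (V = 1.05): implied SD about 36.1. For example, SD = 36 gives n = 83.4, rounded up to 84, and 84 / 0.8 = 105.

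If the 20% loss is applied at each of the three measurements, 105 × 0.8³ = 53.8 are evaluable, and the implied SDs are 39.6 and 28.9. So 105 is compatible with either method, depending on an SD that the article does not state.

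**Step 2: variance factors (one baseline, two follow-ups).**

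- ANCOVA: (1 + r)/2 − r². At r = 0.3: 0.65 − 0.09 = 0.56.
- Mean change from baseline: (1 + r)/2 + 1 − 2r = 1.5(1 − r). At r = 0.3: 1.05.
- Ratio at r = 0.3: 1.05 / 0.56 = 1.875.
- Difference: change minus ANCOVA = 1 − 2r + r² = (1 − r)², which is positive for every r below 1. ANCOVA is always the more precise of the two.

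**Step 3: power if N gives exactly 80% under ANCOVA at r = 0.3.** Effect size, SD and dropout cancel.

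- Mean change at r = 0.3: Φ(2.802 × √(0.56/1.05) − 1.960) = Φ(0.086) = 53.4%.
- Arm-by-time test over three visits (2 df): noncentrality 7.849 × 0.56/1.05 = 4.19, power 43%.
- Other readings of section 2.11.1 at r = 0.3: change at a single visit 43%; group main effect over all three visits 48%.

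Holding N and the effect fixed and varying r:

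| r | V, ANCOVA | V, change | Power, ANCOVA | Power, mean change | Power, arm-by-time (2 df) |
|---|---|---|---|---|---|
| 0.3 | 0.56 | 1.05 | 80% | 53% | 43% |
| 0.5 | 0.50 | 0.75 | 84% | 68% | 57% |
| 0.7 | 0.36 | 0.45 | 94% | 88% | 80% |

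Mean change reaches 80% when 1.5(1 − r) = 0.56, that is r = 1 − 0.56/1.5 = 0.627.

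**Step 4: size of the shortfall in patients.** Under the same condition, 80% power for mean change at r = 0.3 needs 1.875 times the N: 105 × 1.875 = 196.9, about 197 per group instead of 105.

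**The case against.** Three objections carry weight.

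*The method behind 105 is not established.* The ANCOVA sentence is loosely worded and no SD is stated. A change-score calculation with an SD of about 36 also gives 105, and the change analysis would then have its 80%. This stands, and it makes every power figure above conditional. It does not remove the mismatch: ANCOVA is the only method section 2.5 names, and if 105 came from change scores then that section names the wrong one.

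*The correlation is a lower bound.* At higher r the change analysis does better, so 53% is the low end of the stated range. This also stands. But a claim of 80% for any correlation of at least 0.3 has to hold at 0.3. From 0.3 up to 0.7, the range computed, ANCOVA sized at 0.3 stays at or above 80%; mean change does not until about 0.63.

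*A baseline-adjusted model is planned.* A reader might infer that the protocol runs no covariate-adjusted analysis. The document does not support that, because sections 2.10 and 2.11 plan an adjusted regression and will report its effects. However, its baseline term is remission/active status, not the baseline IBDQ score, so it is not the model with the 0.56 factor, and it is not the analysis that section 2.11.1 presents as primary.

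The trial is also called exploratory, and the article condenses a fuller protocol. That lowers the stakes, but the article still claims 80% power and plans significance tests. The conflict lies between two passages that are both printed, so it is not a matter of detail left out.

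**Conclusion.** The inconsistency is real: the stated power is tied to ANCOVA, the primary analysis is repeated measures ANOVA of change from baseline, and no model adjusts for the outcome's own baseline score. Its size depends on how 105 was obtained. If it was set for 80% under ANCOVA at r = 0.3, mean-change power is about 53% at that correlation, rising to about 68% at 0.5 and 88% at 0.7, and the 2-df arm-by-time test has about 43% at 0.3. These figures also rest on a common correlation, a constant effect across follow-ups and, for the mean-change figures, averaging the two changes, which section 2.11.1 does not spell out.

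It would be tempting to conclude that the trial simply has 53% power instead of 80%. The article does not support that unconditional statement, because the SD is missing and 0.3 is a minimum.

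**What to change.** In section 2.11.1, define the primary analysis as the arm difference in the 12- and 24-week scores, with the baseline value of the same score as a continuous covariate (repeated measures ANCOVA, or a mixed model on the two follow-ups). Make the change-from-baseline ANOVA supportive. In section 2.5, state the SD, the effect and the sampsi method that produced 105.

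If change from baseline is kept as primary, the SD and method behind 105 must still be stated, and the power restated for that analysis at the planning correlation. The 53% should not be written in unless the ANCOVA basis is confirmed.

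The preferred change costs wording only. Baseline scores are already collected, and no extra patients or visits are needed. Under the assumptions above, the covariate analysis is more precise than change scores at any correlation below 1, so the change is worth making whichever method produced 105.

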### Random assignment

2.6

Patients will be randomly assigned to the intervention or control group using a stratified block randomization sequence generated by WINPEPI, with the individual as the randomization unit. All IBD patients from the participating centers will be invited to participate in this investigation. An independent administrator will generate the allocation sequence and prepare 210 numbered, opaque, sealed envelopes containing assignments distributed equally between the two study groups. Each participant will be notified via email or the social network of their designated group and given instructions on how to access the relevant app or online survey.

### Study groups

2.7

After obtaining informed consent, the patients will be stratified by disease type, disease activity, and location of outpatient appointments. The participants will then be assigned to the intervention (A) or control (B) group according to the procedure described in 2.7. The groups are described in the following sections.

#### Group A or intervention (gamified mobile‐based tele‐management system)

2.7.1

Participants in the gamified mobile‐based tele‐management system (MyIBD Buddy application) group will receive instructions on using the system and a username and password which will be valid for up to 6 months via standard care. The application was developed for the Android platform using the Suker Wheel game development framework. The research team closely collaborated with the development team and the five‐step ADDIE design model was utilized. The goal was to combine behavior modification strategies and self‐management theory. The educational content of this application has been studied and validated by the research team in our previous work.^16^, ^17^, ^18^, ^19^, ^36^ The study outlines the development process of an application aimed at teaching self‐care techniques, including self‐care skills and psychological aspects such as stress and anxiety control, to monitor patients' physical and mental status, including self‐care skills and psychological aspects such as stress and anxiety control, to monitor patients' physical and mental status, relaxation and mindfulness techniques.

The main functionalities of the MY IBD Buddy application include the following components (Figures 2, 3, 4):
Login page includes user information and disease registration.Patient disease profile (clinical disease history, body mass index calculator).Tele‐monitoring, including five components (tracking symptoms related to IBD):
1.Interaction monitoring (assessing satisfaction with the application).2.Psychological and mental health monitoring (monitoring anxiety and depression, IBD quality of life, and IBD self‐efficacy).3.Medical monitoring (disease activity using disease activity and providing feedback, fecal calprotectin levels monitoring).4.Educational monitoring (assessing knowledge related to the IBD).5.Nutritional monitoring (food diary).
Medication management (medication registration, viewing medication information, setting medication reminders, verifying IBD‐medication interactions, approved and unapproved medication for IBD patients, authorized and unauthorized medication during pregnancy and breastfeeding for patients with IBDs).Laboratory management (manual and visual entry of tests).Colonoscopy readiness program (list and electronic form of precolonoscopy tasks along with setting reminders, comprehensive pre‐ and postcolonoscopy instructions).Tele‐education (self‐care education for managing IBD, and psychological education).Support module (clinical engagement with gastroenterology and mental health experts, technical support for the app, and discussion forum for individuals with IBD).

